### 2.11. Statistical Methods

#### 2.11.1. Sample Size Calculation

The proposed study is a RCT whose primary aim is to investigate the feasibility to recruit and treat participants with AD with acupuncture and to evaluate acupuncture's antipruritic effects. We will calculate the effect sizes of key outcomes including itch VAS and SCORAD index, to inform power calculations for a further large-scale study. A total of 30 individuals with AD and 20 healthy controls will be recruited during the study period; participants with AD will be randomly assigned in a 1 : 1 : 1 ratio to one of two active acupuncture regimens or sham acupuncture. Healthy controls will not receive any treatment. Considering an estimated 20% dropout rate, we identified the sample size with the advice of a statistician. The statistical significance level will be set at 0.1 considering the applied small size.

#### 2.11.2. Statistical Analysis Plan

We will perform descriptive analyses for all outcome measures. Categorical variables will be provided with percentages, and continuous variables will be provided as means with standard deviations. An independent statistician will perform statistical analyses using SPSS 21.0 (IBM SPSS Statistics, New York, USA). Missing data will be replaced by carrying forward the most recent nonmissing value, and the time and reason for the missing data will be recorded. Depending on the recorded reasons, multiple imputation by an independent statistician will be done and compared.

The effectiveness of the intervention will be provided by examining changes in outcome measures between baseline and end of treatment and through the follow-up period, using a repeated measures analysis of variance (ANOVA) and *χ*^2^ test. The difference in effect between VA1 and VA2 will be analysed by examining changes in the itch VAS and SCORAD index, by the Mann–Whitney *U* test on continuous variables and *χ*^2^ test on categorical variables. The difference in therapeutic effect between VA (using the most efficacious dose between VA1 and VA2) and SA will be investigated in the same way. The data will be analysed with a *p* = 0.1 (two-sided) statistical significance level and 90% confidence intervals will be provided following the statistician's advice for a small sample size. The current data will be used to calculate the number of participants needed to reach a significance level of 0.05 and 80% power.

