#### 2.8.2. Verum Acupuncture Group 1 (VA1)

Participants assigned to the VA1 will receive 12 acupuncture sessions over 4 weeks, that is, 3 days/week. A telephone interview will take place two weeks after the end of treatment to collect data on the severity of pruritus symptoms, amount of TCS used, and adverse effects. Participants' final visit will occur 4 weeks after the end of treatment. No other intervention will be permitted during the study period.

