#### 2.8.3. Verum Acupuncture Group 2 (VA2)

Participants assigned to the VA2 will receive 8 acupuncture sessions over 4 weeks, that is, 2 days/week. A telephone interview will be given two weeks after the end of treatment to collect data on the severity of pruritus symptoms, amount of TCS used, and adverse effects. Participants' final visit will occur 4 weeks after the end of treatment. No other intervention will be permitted during the study period.

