### 2.9. Compliance and Discontinuation

During the study period, each patient will receive either 12 or 8 treatment sessions according to their group assignment. Since frequent hospital visits may be the burden to participants and may induce them to withdraw from the trial, we identified a minimum number of treatments to be considered compliant, as follows: at least 10 sessions of 12 should be completed for VA1, and at least 6 sessions of 8 should be completed for VA2 and SA. For dropouts who did not fulfil the aforementioned compliance criteria, last available data will be taken for the analysis.

The study coordinator will maintain regular contact and encourage participants to complete all treatment sessions and follow-up visits. Should a participant withdraw consent, any data collected from the participant will be kept in files safely for 3 years and then will be discarded.

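### Last observation carried forward leads the missing-data handling; it can distort the VA1–VA2 comparison if dropout is unequal, shrinks true differences, and dilutes relapse at week 8

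*Protocol article*

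**What the plan says.** Section 2.11.2 gives the general rule without condition: "Missing data will be replaced by carrying forward the most recent nonmissing value". The time and reason of each gap are recorded, and then: "Depending on the recorded reasons, multiple imputation by an independent statistician will be done and compared". Section 2.9 deals with dropouts who miss the compliance minimum (10 of 12 sessions in VA1, 6 of 8 in VA2 and SA): "last available data will be taken for the analysis".

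The same section explains the compliance minimum by saying that "frequent hospital visits may be the burden to participants and may induce them to withdraw from the trial". VA1 patients "will receive 12 acupuncture sessions over 4 weeks" (2.8.2), VA2 patients "will receive 8 acupuncture sessions over 4 weeks" (2.8.3), and SA has the VA2 schedule (2.8.4). The sample size section uses one overall figure, "Considering an estimated 20% dropout rate", with no split by arm.

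The filled data then enter three analyses in 2.11.2: a repeated-measures ANOVA through follow-up, a Mann–Whitney test of VA1 against VA2 on change in itch VAS and SCORAD, and a Mann–Whitney test of the more efficacious verum arm against SA.

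**The concern.** LOCF treats a patient who leaves during treatment as if symptoms stayed at the last recorded level, and the filled value is analysed as if observed. If patients improve over the four weeks, an early leaver is credited with only part of the improvement. An arm that loses more patients early then looks worse for that reason alone. Here the plan's own reason for withdrawal, visit burden, is heavier in VA1.

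The error would spread. The VA1–VA2 result selects the arm compared with SA and the arm used in the microRNA analysis (2.10.14). The effect sizes for itch VAS and SCORAD are meant to power the next trial (2.11.1).

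Follow-up raises a separate problem. The Background calls the disease relapsing. Table 2 schedules nothing between weeks 4 and 8 except the week-6 telephone interview, which covers itch VAS, topical corticosteroid (TCS) use and adverse events. A missing week-8 SCORAD, EASI, POEM or DLQI is therefore filled with a value from week 4 or earlier. The same holds for biomarkers if the rule is applied to them, and 2.10.13 reads the week 4 to week 8 change in biomarkers as evidence of sustained effect.

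**Working it through.** **Inputs from the protocol article.** 30 patients, 1:1:1, so 10 per arm; 20% dropout overall, leaving 30 × 0.8 = 24, or 8 per arm; 12 versus 8 sessions; two-sided significance level 0.1. No effect size, SD or power is given, so there is no planned effect to reproduce.

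**Assumptions, for illustration only.** Itch falls linearly by T points (0–10 scale) over 4 weeks. A share d drops out with the last value at week L. Either all leave at week 2, or last values are spread evenly over weeks 0 to 3 (mean L = 1.5).

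**Mean improvement under LOCF:** T × [1 − d × (1 − L/4)].

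*No true difference, T = 2 in both arms, L = 2.*
- VA1, d = 0.30: 2 × (1 − 0.15) = 1.70.
- VA2, d = 0.10: 2 × (1 − 0.05) = 1.90.
- False difference: 0.20 points against VA1. At 20%/20% both arms give 1.80 and the difference is 0.

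*True 1.0-point advantage of VA1 (T = 3 versus 2), equal 20% dropout.*
- L = 2: 2.70 − 1.80 = 0.90.
- L = 1.5: 2.625 − 1.75 = 0.875.

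At a fixed SD, the next trial's sample size scales with 1/effect². A shrinkage to 0.90 inflates it by 1/0.81 = 1.23, and a shrinkage to 0.875 by 1/0.766 = 1.31.

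**Simulation of the planned Mann–Whitney test.** 10 per arm, two-sided 0.1, 4,000 runs, dropout completely at random, last values spread evenly over weeks 0–3, assumed SD of 0.3 points per week between patients' slopes and 0.8 points for visit error.

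| Dropout VA1/VA2 | False difference, formula (L = 2; L = 1.5) | Rejection rate, no true difference | Mean LOCF estimate of a true 1.0 | Power for a true 1.0 |
|---|---|---|---|---|
| none | 0; 0 | not run | 1.01 | 0.34 |
| 20%/20% | 0; 0 | 0.088 | 0.87 | 0.27 |
| 30%/10% | 0.20; 0.25 | 0.116 | 0.57 | 0.16 |
| 40%/10% | 0.30; 0.375 | 0.134 | 0.37 | 0.11 |

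Because dropout was completely at random, the observed completers recovered about 1.0 in every scenario with a true difference. Mixed models and multiple imputation were not simulated. The power column therefore shows what LOCF delivers, not how much another method would regain.

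**Follow-up.** Each patient seen at week 4 but not week 8 is assigned zero change. Reported mean relapse = true mean relapse × (1 − share missing). A true 1-point relapse is reported as 0.9, 0.8 or 0.7 with 10%, 20% or 30% missing. For itch VAS and TCS use, the carried value may be the week-6 telephone report, which is already off treatment.

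**The case against.** Several arguments on the other side have force.

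- *The bias depends on the dropout pattern.* The plan gives no split by arm, and 30% versus 10% is 3 patients against 1. Someone might infer that LOCF necessarily biases VA1 against VA2. The documents do not support this: with equal dropout and equal trajectories the bias is zero.
- *The size is modest for this trial.* If the itch SD is 1.5 to 2.5 (assumed), the standard error of a difference with 10 per arm is SD × √(2/10) = 0.67 to 1.12, so 0.2 points is about 0.2 to 0.3 standard errors. The false-positive rate at 30%/10% is 0.116 against 0.10. This stands for the test of no difference. It does not answer the shrinkage of true effects, and effect estimation is what the trial is for.
- *Hidden relapse.* It is tempting to say that LOCF conceals relapse and biases the study toward a sustained effect. Relapse is only diluted, by the share missing. Benefit from baseline to week 8 can go either way: a week-2 leaver with 1.0 point carried, whose true course was a 2-point fall and then a relapse, has the benefit understated if the relapse is below 1 point and overstated if it is above.
- *Narrow intervals.* It might also be inferred that filled values make the intervals too narrow. No interval coverage was calculated, and the simulated rejection rate at 20%/20% was 0.088, below nominal.
- *Multiple imputation is planned.* It is, and this mitigates the problem. But it is conditional and secondary to the stated lead rule. The imputation model may properly sit in a document not shown; the choice of lead rule is stated here.
- *The target effect.* The Discussion counts acceptability as part of choosing a schedule, so a lower benefit in an arm that patients leave is false only if the target is the effect had they continued. That is fair, but LOCF does not give the alternative target either, unless symptoms really stay frozen after leaving.

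Nor do the documents say that outcome assessment stops when treatment stops. Section 2.9 has the coordinator encourage patients to complete follow-up visits.

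**Conclusion.** The concern holds in a conditional form. LOCF is the stated lead rule in both 2.9 and 2.11.2, and the plan names a cause of withdrawal that differs by arm. Under linear improvement of 2 points and dropout at week 2, 30%/10% dropout produces a false difference of 0.2 points; equal dropout with equal trajectories produces none. If the schedules truly differ, the difference shrinks even at equal 20% dropout, from 1.0 to about 0.87–0.9, and that estimate goes into the next trial's sample size. For patients seen at week 4 and missing at week 8, week 4–8 change is set to zero for SCORAD, EASI, POEM and DLQI, and for biomarkers if the rule covers them; 20% missing leaves 80% of the mean relapse visible.

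The arm-specific dropout rates, the linear course and the SDs are assumptions. The exploratory label limits the weight of any test result but not the need for unbiased effect estimates. The change is worth making before unblinding.

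**What to change.** In 2.9 and 2.11.2, replace LOCF as the lead rule.

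- **Main analysis:** a likelihood-based repeated-measures model on all observed visits (weeks 1, 2, 3, 4 and 8, plus week 6 for itch VAS), with arm, visit, arm-by-visit, baseline as a single covariate, a simple covariance structure and small-sample degrees of freedom. Take the VA1–VA2 and VA–SA contrasts at weeks 4 and 8 from this model, with the planned 90% confidence intervals. Changing only the ANOVA would leave the two Mann–Whitney comparisons without a missing-data rule.
- **Keep it small:** three arms by five visits plus one baseline term is 16 mean parameters. A baseline-by-visit interaction would make it 20 (24 with week 6), which is heavy for 30 patients.
- **Supportive:** the Mann–Whitney tests, on observed or multiply imputed changes.
- **Sensitivity:** multiple imputation, run whatever the recorded reasons. It also brings in patients with a baseline value only, who do not contribute to the model. LOCF at most as a further sensitivity analysis.

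The cost is a change of wording and a little more analysis work; the visits are already scheduled. The downside is reliance on a missing-at-random assumption and on a simple covariance structure with 10 patients per arm.

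### The between-arm test is fixed as an unadjusted Mann–Whitney on change scores: valid, but a baseline-adjusted mean difference would fit the trial's estimation aim better, with a modest gain in precision

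*Protocol article*

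**What the plan says.** Section 2.11.2 sets the comparison of the two verum schedules: "The difference in effect between VA1 and VA2 will be analysed by examining changes in the itch VAS and SCORAD index", using the "Mann–Whitney *U* test on continuous variables". For the better verum arm against sham, the difference between that arm "and SA will be investigated in the same way". Neither sentence names a baseline covariate. The same section plans a repeated measures ANOVA over time and means with standard deviations. It also fixes the level: "The data will be analysed with a *p* = 0.1 (two-sided) statistical significance level". Of the intervals it says that "90% confidence intervals will be provided following the statistician's advice for a small sample size".

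Section 2.11.1 gives the size: "A total of 30 individuals with AD and 20 healthy controls will be recruited during the study period". The 30 patients are split equally over three arms, so 10 per arm, with 20% dropout expected. That section also says that effect sizes for itch VAS and SCORAD will be calculated to plan a larger trial. Section 2.11.2 adds that the data will be used to size a trial with 80% power at 0.05. Table 2 schedules both outcomes at baseline, weekly to week 4, and at week 8.

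**The concern.** The main product of this feasibility trial is an estimate, its interval and a standard deviation for planning. The between-arm method that the article fixes is a rank test, whose direct output is a p-value.

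Three features make it a weak match:

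- Subtracting baseline forces the slope of follow-up on baseline to be 1. If the true slope is lower, a chance baseline difference between arms of 10 passes into the contrast through regression to the mean.
- The exact rank test cannot reach the nominal 0.10 in arms this small, so part of the liberal level chosen for the small sample is lost.
- The test and the promised estimates are separate analyses, so p-value and interval need not agree.

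At stake is some power and precision in a very small trial, and a planning estimate that does not come from the model that tests it. Validity is not at stake.

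**Working it through.** **Inputs from the article.** 10 per arm (30 over three arms); 8 completers at 20% dropout (10 × 0.8 = 8), although values carried forward may keep the analysed number at 10; two-sided level 0.10; baseline itch above 3 and below 8 (section 2.4.1). The article gives no power, SD or effect size for this trial, so there is no plan figure to reproduce.

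**Assumptions.** Itch with underlying mean 5.5 and SD 1.8, normal; true difference 1.5 points; correlation rho between baseline and follow-up before restriction, from 0.3 to 0.8.

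**1. Level of the exact Mann–Whitney test.** At 10 per arm it rejects at U ≤ 27, a two-sided level of 0.089. At 8 per arm it rejects at U ≤ 15, level 0.083.

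**2. Variance ratio, ANCOVA to change score, without entry limits.** With equal SDs and large samples: (1 − rho²) / [2(1 − rho)] = (1 + rho)/2, which is 0.65 at rho 0.3 and 0.75 at rho 0.5. These values do not apply here, because entry limits make the baseline SD smaller than the follow-up SD.

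**3. The same ratio with entry limits.** Cutting baseline to 3–8 reduces its SD from 1.8 to about 1.265 (variance about 1.60). The slope of follow-up on baseline stays at rho.

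- ANCOVA residual variance: 3.24(1 − rho²)
- Change-score variance: 3.24(1 − rho²) + 1.60(1 − rho)²
- Small-sample factor on ANCOVA for chance imbalance: 1 + 1/(2n − 4) = 1.0625 at n = 10

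| rho | ANCOVA | Change | Ratio | × 1.0625 |
|---|---|---|---|---|
| 0.3 | 2.95 | 2.95 + 0.78 = 3.73 | 0.79 | 0.84 |
| 0.5 | 2.43 | 2.43 + 0.40 = 2.83 | 0.86 | 0.91 |
| 0.7 | 1.65 | 1.65 + 0.14 = 1.80 | 0.92 | 0.98 |
| 0.8 | 1.17 | 1.17 + 0.06 = 1.23 | 0.95 | 1.01 |

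Simulation of the same set-up gives 0.83–0.84 at rho 0.3, 0.90–0.91 at 0.5, 0.98 at 0.7 and 1.01 at 0.8. The gain is therefore about 17%, 10%, 2% and none. Restricting entry on baseline shrinks the benefit of adjustment (0.65 becomes 0.79, and 0.75 becomes 0.86, before the small-sample factor).

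**4. Simulated power, 10 per arm, level 0.10.**

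| rho | Mann–Whitney on change | t-test on change | ANCOVA |
|---|---|---|---|
| 0.3 | 47% | 51% | 57% |
| 0.5 | 56% | 60% | 64% |
| 0.7 | 73% | 78% | 78% |
| 0.8 | 87% | 90% | 89% |

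At 8 per arm, Mann–Whitney against ANCOVA is about 37% against 48% (rho 0.3) and 46% against 54% (rho 0.5). ANCOVA's false-positive rate stayed at about 10%. The t-test column splits the gap: at rho 0.3, 4 of 10 points come from ranks and discreteness, and at rho 0.5, 4 of 8. At 0.7 and above, essentially all of it does.

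**5. Interval from the rank test.** Inverting Mann–Whitney (Hodges–Lehmann) does give an interval in scale units. With equal SDs, no entry limits, n = 10 and rho 0.5, its mean width is 1.64 SD with about 91% coverage, against 1.37 SD for ANCOVA.

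**The case against.** The best defence is that a rank test is valid and reasonable at 8 to 10 per arm, where normality and linearity are hard to check. The study is exploratory, with no primary outcome (section 2.10), and a repeated measures ANOVA is planned alongside. All of that stands. It is also true that a journal article may leave the estimator behind the 90% interval to a fuller plan, so its silence there is not a fault. The point rests on the test that the article does name.

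A reader might infer four stronger things that the documents do not support:

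- *Baseline information is thrown away.* A change score uses baseline, with the slope set to 1.
- *No interval or SD will be available.* Section 2.11.2 promises both, and the rank test can be inverted to give an interval in scale units.
- *The entry limits make change scores especially noisy.* Step 3 shows the reverse: they reduce what adjustment gains.
- *ANCOVA is plainly and freely more precise.* It costs one degree of freedom and a linearity assumption, and the gain depends on a correlation that is not stated. If the follow-up SD were 1.5 times the baseline SD with correlation 0.5 in the enrolled patients, the large-sample ratio would be 0.96. With a true slope of 1 it would be 1.00.

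**Conclusion.** The concern holds as a modest efficiency and estimation improvement. The planned test controls error and is somewhat conservative. For a trial whose output is effect sizes, a baseline-adjusted mean difference is the better main estimate. It gives estimate, interval and planning SD from one model, and under the assumptions above it had higher power than the planned test at every correlation tried: 10 points at rho 0.3, falling to 2 at rho 0.8. Only part of that is due to adjustment. The size rests on the assumed SD, difference, correlation and normal data, none of which the documents supply. At high correlation there may be no variance gain at all.

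**What to change.** In section 2.11.2, or in the full analysis plan, make the main between-arm estimate for itch VAS and SCORAD at weeks 4 and 8 the mean difference adjusted for the baseline value, from ANCOVA or the week-specific contrast of a mixed model. Report it with its 90% confidence interval and the residual SD, and use these for planning the larger trial. Keep Mann–Whitney on change as a sensitivity analysis, which guards against non-normality or non-linearity in small arms.

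The cost is a change of wording; both baselines are already scheduled in Table 2. The price in the analysis is one degree of freedom and a linearity assumption.

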#### 2.10.14. Exploring Biomarkers with MicroRNA Expression Profiling

AD is known as a complex genetic skin disease affected by environmental distress and resulting from abnormal immune responses as well as malfunctions of the skin barrier [50, 61]. But no specific biomarker for the diagnosis of atopic disorder has yet been identified [50, 51]. In this context, microRNA (miRNA) will be analysed in order to explore new candidates associated with the development of AD and its treatment with acupuncture.

A miRNA is a small noncoding RNA molecule. Since its function is related to eukaryotic cells, dysregulation of several specific miRNAs has been reported to be associated with several pathological processes, such as chronic lymphocytic leukemia and cardiomyopathy [62, 63]. In the study of AD, some miRNAs were proposed to be related to AD symptoms [64, 65], but none has been confirmed as a predictive or prognostic marker.

Illumina sequencing using serum will be performed for miRNA expression profiling to determine candidate miRNA biomarkers for the effectiveness of acupuncture. The difference between participants with AD and healthy controls at baseline will be analysed to explore potential biomarkers associated with the development of AD. Within the pool of biomarker candidates related to AD, the difference between VA1 or VA2 (whichever is more efficacious) and SA at 4 weeks will be compared, to determine biomarkers related to acupuncture effect. The difference between VA and SA at 8 weeks will also be analysed to examine whether the selected biomarkers at 4 weeks continue to be significant at 8 weeks, to explore sustained effects of acupuncture (Figure 2).

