**Figure 2 fig2:**

*Flow of Illumina sequencing*. AD, atopic dermatitis; VA, among VA1 and VA2, the most effective schema will be selected; SA, sham acupuncture group; wks, weeks. A tube icon means the sera obtained from the blood samples.

**Table 1 tab1:** Acupuncture treatment details based on the STRICTA 2010 checklist.

Item	Detail
*(1) Acupuncture rationale*	*(1a) Style of acupuncture* (i) MA and IA using PTN based on traditional meridian theory *(1b) Reasoning for treatment provided, based on historical context, literature sources, and/or consensus methods, with references where appropriate* (i) Partially individualised MA treatments and IA treatments based on the traditional meridian theory, clinical experience, and consensus by the experts in acupuncture and AD *(1c) Extent to which treatment was varied* *MA*: Partially individualised, that is, fixed points plus optional points according to symptoms *IA*: Fixed treatment

*(2) Details of needling*	*(2a) Number of needle insertions per subject per session (mean and range where relevant)* *MA*: From 6 to 19 body acupoints per participant per session *IA*: 2 body acupoints and 1 auricular acupoint per participant per session *(2b) Names (or location if no standard name) of points used (uni/bilateral)* *MA*: (i) Fixed points: PC6, LI11, ST36 bilaterally (ii) Optional points: ST43, GB41, LI2, TE3, TE6, SI2, SI3, BL66, LR3, SP3 contralaterally (GB41, TE3, SI3 can be applied bilaterally according to the signs or symptoms of the patient) *IA*: LI11 bilaterally and auricular shenmen contralaterally *(2c) Depth of insertion, based on a specified unit of measurement or on a particular tissue level* *MA*: From 5 to 30 mm, perpendicular to skin surface *IA*: 1.5 mm, perpendicular to skin surface *(2d) Response sought (e.g., de qi or muscle twitch response)* *MA*: “de qi” sensation *IA*: None *(2e) Needle stimulation (e.g., manual, electrical)* *MA*: Manual stimulation, needle rotation with thumb and index fingers for the first 10–15 seconds *IA*: Participants will be educated to press PTNs for 3 seconds when they feel severe itch *(2f) Needle retention time* *MA*: 15 minutes *IA*: 1-2 days or until PTN falls off *(2g) Needle type (diameter, length, and manufacturer or material)* *MA*: A sterilised stainless steel needle (0.25 × 40 mm, Dongbang Acupuncture Inc., Bundang, Seongnam, Korea) *IA*: A hypoallergenic PTN (1.5 mm, 10 × 10 mm adhesive tape, Haeng Lim Seo Won Medical Co., Korea)

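### The only described pairwise verum-versus-sham comparison uses whichever verum arm looked better in the same patients, so its estimate is biased toward acupuncture

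*Protocol article*

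**What the plan says.** Section 2.11.2 of the protocol article takes two steps. First, "The difference in effect between VA1 and VA2 will be analysed by examining changes in the itch VAS and SCORAD index". Second comes the comparison with sham, worded as the difference "between VA (using the most efficacious dose between VA1 and VA2) and SA will be investigated in the same way". Both steps use the level set in that section: "The data will be analysed with a *p* = 0.1 (two-sided) statistical significance level and 90% confidence intervals will be provided".

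The same choice of arm recurs in the microRNA work. Section 2.10.14 states that "VA1 or VA2 (whichever is more efficacious) and SA at 4 weeks will be compared", and the Figure 2 legend has "VA, among VA1 and VA2, the most effective schema will be selected".

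On size, section 2.11.1 states that "A total of 30 individuals with AD and 20 healthy controls will be recruited during the study period", with the patients "randomly assigned in a 1 : 1 : 1 ratio to one of two active acupuncture regimens or sham acupuncture", and allows for 20% dropout. Sections 2.11.1 and 2.11.2 also say that effect sizes and data from this trial will feed the power calculation of a larger one, at 0.05 and 80% power.

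Section 2.2 expects the three-times-weekly schedule to do better, but section 2.11.2 does not fix that arm as the one compared with sham. The article describes no independent data for the choice, no adjustment for it, and no single outcome or time point that decides it.

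**The concern.** Suppose two arms have the same true effect. The one with the better observed mean is, on average, the one that chance favoured. Comparing that arm with sham on the same data passes the luck on to the estimate. The sham arm gets no such selection, so the error always points toward acupuncture.

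Two things are at stake. One is the reading of the VA-SA result and its 90% CI. The other is the main trial: an inflated effect size gives too small a sample. Exploratory status softens the first but not the second, because informing the next trial's size is a stated purpose of this one.

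**Working it through.** **The plan's own figure.** No effect size, SD or power is given for the 30 patients, so a power formula cannot reproduce that number. Only the dropout step can be checked: 24 / (1 - 0.20) = 30, or 8 completers becoming 10 per arm. The base of 24 is not stated.

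**Inputs.** From the article: 10 per arm (30 patients, 1:1:1), or 8 per arm after 20% dropout; Mann-Whitney U test, two-sided 0.10; main trial at 0.05 and 80% power. Assumed: normal changes with equal SD, the arm picked on the larger mean change in the outcome being analysed, a two-sided 0.05 for the main trial, and the true effects used below.

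**Bias.** Let n be the number per arm, delta the true gap between VA1 and VA2 in SD units, and tau = sqrt(2/n) the standard error of their observed difference. The selected arm's mean exceeds its own true value on average by tau × phi(delta/tau), where phi is the standard normal density. With delta = 0 this is 1/sqrt(pi × n).

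| True gap | n = 10 (tau = 0.447) | n = 8 (tau = 0.500) |
|---|---|---|
| 0 | 0.447 × 0.399 = 0.178 SD | 0.500 × 0.399 = 0.199 SD |
| 0.3 SD | 0.447 × 0.319 = 0.142 SD | 0.500 × 0.333 = 0.167 SD |
| 0.5 SD | 0.447 × 0.214 = 0.095 SD | 0.500 × 0.242 = 0.121 SD |

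Simulation of 100,000 trials per scenario agrees. At n = 10 it gives 0.177 to 0.180 SD for equal arms, 0.144 SD for a gap of 0.3 (true effects 0.5 and 0.2, or 0.8 and 0.5) and 0.094 SD for a gap of 0.5 (0.8 and 0.3).

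**Error rates when neither schedule works (same simulation).**

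| | Fixed arm | Selected arm |
|---|---|---|
| n = 10, any rejection | 8.9% | 8.9% |
| n = 10, verum better | 4.4% | 7.7% |
| n = 8, any rejection | 8.3% | 8.3% |
| n = 8, verum better | 4.1% | 7.2% |

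With exact Mann-Whitney p-values (40,000 trials), the verum-better rate goes from 4.2% to 7.5% at n = 10 and from 4.1% to 7.3% at n = 8. A t-based 90% CI for the selected difference still covers about 90%, but at n = 10 its lower limit lies above the truth in 8.6% of trials instead of 5%.

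**Main-trial size, if the selected estimate is used.** n per arm = 2 × (1.960 + 0.842)² / d² = 15.70 / d², rounded up. True power = Phi(d × sqrt(n/2) - 1.960), where Phi is the standard normal distribution function. The planning value is the true d plus the worst-case bias of 0.178.

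| True d (assumed) | n needed | Planning d | n planned | True power |
|---|---|---|---|---|
| 0.3 | 175 | 0.478 | 69 | 42% |
| 0.5 | 63 | 0.678 | 35 | 55% |
| 0.8 | 25 | 0.978 | 17 | 65% |

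With 8 per arm (bias 0.199) the planned n is 63, 33 and 16, and true power 39%, 53% and 62%. A t-based calculation at d = 0.5 gives 64 and 36 per arm, and again 55% power.

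**The case against.** The strongest reply is that this is an exploratory feasibility trial with no primary outcome (section 2.10), and that finding a good schedule is one of its aims (section 2.1). Some selection is intended, and choosing a schedule for the next trial is legitimate. That stands. The fault lies only in carrying the winner's unadjusted estimate into inference or sizing.

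Several stronger readings are tempting, but the article does not support them:

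- **That the main efficacy result is biased.** No main contrast is named. The first effectiveness analysis in section 2.11.2 is a repeated measures ANOVA with a chi-square test, and it is not described as using a selected arm.
- **That the other verum arm is never set against sham.** Descriptive results are planned for all outcomes, and section 2.10.13 plans between-group biomarker comparisons with no selection stated. Only the pairwise test for the other arm is undescribed.
- **That the trial's type I error is inflated.** Total two-sided rejection does not change; the error moves into the favourable tail.
- **That 0.18 SD is the expected bias.** It is the equal-arms case. Section 2.2 expects the schedules to differ, and the bias is then smaller.
- **That the selected contrast will size the main trial.** Sections 2.11.1 and 2.11.2 refer to effect sizes of key outcomes and to the current data. They do not name this contrast, although it is the only pairwise verum-sham contrast described.
- **That the same bias applies to the microRNA results.** Selection there is on efficacy, so any distortion depends on an unknown correlation between efficacy and each microRNA.

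It is also fair to say that a fixed-arm estimate would be a weak basis for sizing. At 10 per arm its standard error is sqrt(2/10) = 0.447 SD and its 90% CI about ±0.78 SD, so the largest bias is 0.178/0.447, about 0.4 standard errors. But that imprecision runs in both directions; the selection bias runs in one.

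**Conclusion.** The point holds for the pairwise VA-SA comparison in section 2.11.2. As written, its estimate is biased toward acupuncture whatever the true gap between the schedules. The size of the bias rests on normal data with equal SD and on picking the arm by the outcome analysed.

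The harm to significance testing is modest and lies in the direction of the errors. The harm to sizing could be substantial, but it is conditional: it needs the selected contrast to be the planning input, and the power figures use assumed true effects and the worst-case bias. For the microRNA comparison the selection is real but its effect cannot be quantified from the article. This should be corrected before the data are unblinded; it does not undermine the trial's other analyses.

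**What to change.** In section 2.11.2, replace the selected-arm comparison with VA1-SA and VA2-SA. Report both with 90% CIs whichever looks better, Dunnett-adjusted if a test is claimed. Before unblinding, name the contrast whose effect size will go into the main-trial calculation: one verum arm, the pooled verum arms, or a selection-adjusted estimate. Choosing a schedule for the next trial may remain an aim, with a statement that the winner's unadjusted estimate is not used for inference or sizing.

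In section 2.10.14 and Figure 2, compare both verum arms with sham if both are sequenced; otherwise label the result as conditional on post hoc arm selection.

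No extra patients are needed, and for the clinical outcomes the change is one of wording. The price is two contrasts instead of one, slightly wider intervals if adjusted, and a less favourable effect size. The microRNA cost is unclear. The abstract speaks of profiling each group, but the Figure 2 legend puts the selection inside the sequencing flow. If only the chosen arm's later samples were to be sequenced, comparing both arms would add laboratory work; the label would not.
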